### Sample Size Justification

To estimate a 5% precision for postoperative hernia incidence with 95% CI, a minimum of 255 cases is required. For port-site hernias, at least 188 patients are required; for parastomal hernias, 349. For secondary outcomes, the required sample sizes are 255 for SSI and 93 for burst abdomen. Sample size considerations are summarised in Table 1. To detect a moderate effect size (Cohen’s d = 0.3) with 80% power at α = 0.05, the required sample size is.
• Chi-squared test (1 df): 88 patients
• Chi-squared test (5 df): 143 patients
• Student’s t-test: 102 patients

**TABLE 1 T1:** Sample size rationale.

Endpoint	Sample size	Notes
Incisional Hernia	255	To estimate with 5% precision, 95% CI
Port-site Hernia	188	To estimate with 5% precision, 95% CI
Parastomal Hernia	349	To estimate with 5% precision, 95% CI
Surgical Site Infection (SSI)	255	To detect moderate effect size, 80% power
Burst Abdomen	93	To detect moderate effect size, 80% power

The total planned cohort will consist of 500 patients, which ensures sufficient power to assess primary and secondary outcomes while allowing for exploratory and subgroup analyses, including risk factors associated with specific surgical techniques or patient characteristics. This sample size also accommodates a potential dropout rate of up to 10% and supports the development of multivariate models with adequate statistical reliability.

To ensure feasibility across all participating centres, over-recruitment will be limited to a maximum of 50% above the calculated minimum sample size required for primary endpoints.

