Numerous studies and guidelines have investigated factors influencing hernia formation. Patient-related risk factors include diabetes, obesity, chronic pulmonary disease, immunosuppression, and a history of abdominal surgeries [7]. The guidelines of the European Hernia Society emphasize the need for further research into methods of preventing the occurrence of postoperative hernias [2]. Procedure-related factors such as the type of incision, suture material, fascial closure technique, and use of surgical drains also play a role in hernia pathophysiology [1, 4, 8]. The World Society of Emergency Surgery (WSES) and European Hernia Society (EHS) guidelines recommend the “small bites” technique for fascial closure using slowly absorbable sutures, although most of the supporting evidence is derived from elective surgery [1, 9]. Despite these recommendations, high-quality prospective data focusing exclusively on emergency surgery settings are limited. These guidelines highlight the importance of conducting prospective studies to establish the efficacy of this technique in urgent and emergency surgical procedures [1].

Management of surgical wounds and abdominal wall closure in the emergency setting remains highly variable, with limited evidence guiding best practice. Surgical site infection—affecting approximately one-third of patients undergoing emergency procedures—is also a well-established risk factor for postoperative hernia development [2, 7] A less common but clinically significant complication, which also contributes to hernia formation, is wound dehiscence or evisceration [10]. Therefore, prevention of such early postoperative complications is crucial in reducing the risk of subsequent hernia formation. Furthermore, there is a lack of consensus regarding the effectiveness of postoperative interventions aimed at hernia prevention, such as the use of abdominal binders or recommendations concerning the timing of return to full physical activity [9].

Given the substantial clinical burden posed by postoperative hernias and the paucity of targeted data in emergency surgery, the PROPHECY trial aims to quantify hernia incidence and assess modifiable perioperative risk factors within this high-risk cohort.

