Parastomal hernias remain another prevalent but under-reported complication. A study by Antoniou et al. found that up to half of patients with permanent stomas develop a hernia at the stoma site [6]. Evidence supports the use of prophylactic mesh in elective stoma formation to reduce this risk [6, 13], but the safety and feasibility of mesh use in emergency stoma creation is still debated due to concerns regarding infection. A meta-analysis by Elzeftawy et al. demonstrated that mesh implantation—particularly in the retromuscular position—significantly reduces the risk of parastomal hernia without increasing the incidence of surgical site infections [13].

One of the most important modifiable factors identified in the literature is surgical site infection (SSI), which significantly increases the risk of incisional hernia development [7, 12]. The use of prophylactic negative pressure wound therapy (NPWT) on closed incisions has shown promise in reducing SSI rates, particularly in high-risk or contaminated fields [14]. Nevertheless, adoption of NPWT in emergency settings remains inconsistent. PROPHECY will capture detailed data on the use of NPWT and its association with hernia and wound-related outcomes.

The inclusion of burst abdomen as a secondary endpoint reflects the growing awareness of this severe complication. Kvist et al. recently reported that burst abdomen following emergency laparotomy occurred in 4.4% of patients and was associated with significantly higher rates of morbidity and mortality [10]. This underlines the importance of optimal fascial closure and early identification of wound dehiscence in this population.

Another area of interest is postoperative care, including the use of abdominal binders and guidance on physical activity resumption. While widely practised, there is limited high-quality evidence supporting their role in preventing hernia formation [2, 9]. PROPHECY will contribute to clarifying the effectiveness of these interventions.

Finally, the multicentre, prospective design and robust sample size calculation of the PROPHECY trial will allow for meaningful subgroup analyses and generalisable conclusions.

By identifying both patient- and procedure-related modifiable risk factors, this study has the potential to inform the creation of specific guidelines for hernia prevention in emergency surgery, where currently none exist.

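### Table 1 credits the SSI (255) and burst-abdomen (93) sample sizes to 80% power, but the article's own sizes for that basis differ, and both fit ±5-point precision at unstated rates

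*Protocol article*

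**What the plan says.** In the Protocol article, Sample Size Justification, the running text first gives sizes for estimating the hernia endpoints to 5% precision: 255 for postoperative hernia, 188 for port-site and 349 for parastomal. It then states that "the required sample sizes are 255 for SSI and 93 for burst abdomen", with no basis of its own. A separate sentence follows: "To detect a moderate effect size (Cohen’s d = 0.3) with 80% power at α = 0.05, the required sample size is". Under it come three entries: "Chi-squared test (1 df): 88 patients", "Chi-squared test (5 df): 143 patients" and "Student’s t-test: 102 patients".

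Table 1 repeats the five endpoint sizes. The three hernia rows are marked as precision-based. The SSI and burst-abdomen rows are marked "To detect moderate effect size, 80% power".

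No planning rate is given for either secondary endpoint. The only rates in the article are background. The Introduction describes SSI as "affecting approximately one-third of patients undergoing emergency procedures", and the Discussion cites a report that "burst abdomen following emergency laparotomy occurred in 4.4% of patients". The Statistical Analysis section reports secondary outcomes as proportions with 95% confidence intervals. The cohort is 500, with allowance for up to 10% dropout.

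**The concern.** Two of the five rows in Table 1 carry a basis that the section's own figures contradict. A reader who takes the table at face value believes that SSI and burst abdomen were sized for a comparison with 80% power. The text order and the numbers point instead to an incidence estimate with a ±5-point margin. These are different claims, and only one can be the source of 255 and 93.

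If precision is the true basis, a second question follows: which rates were assumed? The rates implied by 255 and 93 are not the ones the article quotes. At stake are the reproducibility of the sample size, which the article gives as a reason for publishing the protocol in advance, and an assurance of power for a rare endpoint that the design may not be able to give.

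**Working it through.** **Inputs.** From Sample Size Justification and Table 1: SSI 255; burst abdomen 93; effect 0.3, power 80%, α = 0.05 (taken as two-sided, since the sidedness is not stated); margin ±5 points with 95% CI; cohort 500; dropout up to 10%, so 500 × 0.9 = 450 evaluable. Background rates: SSI one-third (Introduction) and burst abdomen 4.4% (Discussion).

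**1. The power basis.** For a chi-squared test, N = λ/w², where λ is the noncentrality giving 80% power. With w = 0.3:

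- 1 df: 87.2, so 88. This reproduces the article.
- 2 df: 107.1, so 108.
- 5 df: 142.5, so 143. This reproduces the article.
- 25 df: 253.9, so about 25 df would be needed to reach 255.

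93 falls between the 1 df and 2 df values. Inflating 88 for 10% dropout gives 98, one-sided testing gives 69, and 90% power gives 117. A two-sample t-test at d = 0.3 needs 176 per group. No plausible variant for a binary endpoint gives 255 or 93. (The listed t-test size of 102 does not follow from d = 0.3 either. That is a separate matter.)

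**2. The precision basis.** N = 1.96² × p(1 − p)/0.05².

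- p = 0.21: 254.9, that is 255.
- p = 0.065: 93.4, that is 93 to the nearest whole number.

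Any N up to 384 solves to some p, so the back-solve alone proves little. Three facts support it: the text places 255 and 93 directly after the precision figures and before the effect-size sentence; the SSI figure equals the incisional-hernia figure, which Table 1 marks as precision-based; and the planned analysis of secondary outcomes is a proportion with its interval.

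**3. Precision at the rates the article quotes.**

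| Endpoint | Rate | N for ±5 points | Stated N |
|---|---|---|---|
| SSI | 30% | 322.7 → 323 | 255 |
| SSI | 1/3 | 341.5 → 342 | 255 |
| SSI | 35% | 349.6 → 350 | 255 |
| Burst abdomen | 4.4% | 64.6 → 65 | 93 |

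Other interval methods do not recover the stated numbers. SSI at one-third needs 339 (Wilson) or 359 (Clopper-Pearson). Burst abdomen at 4.4% needs 77 (Wilson), 86 (Clopper-Pearson) or 88 (Agresti-Coull).

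**4. What the cohort delivers.** Half-width = 1.96 × √(p(1 − p)/n).

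- SSI at 1/3: ±5.8 points at 255, ±4.4 at 450, ±4.1 at 500.
- Burst abdomen at 4.4%: ±4.2 points at 93, ±1.9 at 450. Expected events at 450: 450 × 0.044 ≈ 20.

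**5. Can burst abdomen show an effect of 0.3?** For a binary factor that splits patients evenly, the largest possible phi arises when every event falls in one half: √(0.044/0.956) ≈ 0.21. An effect of w = 0.3 cannot occur there. With all events in an exposed group of share q, phi = 0.3 requires (1 − q)/q = 0.09 × 0.956/0.044 ≈ 1.96, so q is about 34%. Only a factor present in about a third of patients or fewer, with essentially all the events, could reach it.

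**The case against.** The strongest defence is that nothing in the study fails. Four parts of it stand, and each rules out a stronger reading.

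- **A reader might infer that the stated power is absent.** The documents do not support this. At w = 0.3, N = 255 gives 99.8% power at 1 df and 97.5% at 5 df, and it exceeds all three listed sizes. N = 93 gives 82.5% at 1 df, though only 58.7% at 5 df. What is missing is a traceable derivation.
- **A reader might infer that the SSI number is 87 too low (342 − 255).** That holds only if SSI was meant to be estimated to ±5 points at one-third. The article never names one-third as its planning rate. On the basis Table 1 does state, 255 is more than needed.
- **A reader might infer that ±5 points is meaningless for burst abdomen because the interval crosses zero.** At 93 patients and 4.4% the interval is 4.4 ± 4.2, or 0.2% to 8.6%. It crosses zero at 65 patients, which is not the plan's number.
- **The 4.4% is a laparotomy rate.** This cohort also takes appendicitis and cholecystitis and records open and minimally invasive approaches, so the event counts and widths above are conditional on that rate.

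It is also fair that nobody will analyse only 93 patients, and that the regression models are aimed at hernia rather than burst abdomen. This limits the practical harm. It does not rescue the label: condensing a protocol into an article can explain an omitted input, but here a specific basis is printed that the neighbouring figures contradict. Nor does the nominal 82.5% reassure for burst abdomen, because at 4.4% an evenly split factor cannot produce the effect in question.

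**Conclusion.** The point holds as an error of stated basis. The effect-size basis given in Table 1 for SSI and burst abdomen yields 88, 143 or 102 in the article's own list, not 255 or 93. The two numbers are best explained as ±5-point precision sizes at about 21% and 6.5%. This is an inference that the article does not confirm, and those rates differ from the only ones it quotes.

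The two rows miss in opposite directions on the quoted rates: SSI would need about 342 (323 to 350) against 255, and burst abdomen about 65 against 93. Both comparisons assume that the background rates are the planning rates. The 450 evaluable patients cover every SSI figure in that range. Cohort size, endpoints and planned analyses stay as they are. The severity is minor to moderate, and this is not something that must be resolved before the study can proceed.

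**What to change.** In Table 1, and in the sentence that introduces the two numbers:

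1. Mark the SSI and burst-abdomen rows as sized for precision (±5 points, 95% CI), if the authors confirm that basis, and remove the 80% power claim from both.
2. State the rate assumed for each figure and its source.
3. If one-third is the planning rate for SSI, replace 255 with about 342 and note that 450 evaluable patients give about ±4.4 points. If another rate was used, give it and explain why it differs from the Introduction.
4. For burst abdomen, state the precision of the full cohort: about ±1.9 points and about 20 events at 450 if the rate is 4.4%. Say that this rate comes from emergency laparotomy and is an assumption for a mixed cohort. Make no claim of 80% power for a moderate effect on this endpoint.

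The cost is an edit to two table rows and a sentence or two of text. No extra patients, data or analyses are needed.

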### Statistical Analysis

The primary and secondary outcomes will be expressed as proportions with 95% confidence intervals. Continuous variables will be described using medians and interquartile ranges and analysed using Student’s t-test or the Wilcoxon test as appropriate. Categorical variables will be compared using the Chi-squared test. Univariate and multivariate logistic regression models will be applied to identify independent risk factors for postoperative hernia formation. Relative risk (RR) with 95% CI will be calculated. A p-value <0.05 will be considered statistically significant. All analyses will be conducted using R software in RStudio.

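### None of the three sample sizes listed under Cohen's d = 0.3 (102, 88 and 143) follows from that effect size, and the t-test figure is too low by a factor of about three

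*Protocol article*

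**What the plan says.** The Protocol article's Sample Size Justification gives precision-based sample sizes for the endpoints and then turns to hypothesis tests. One stem covers all of them: "To detect a moderate effect size (Cohen’s d = 0.3) with 80% power at α = 0.05". Three figures follow:

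- "Chi-squared test (1 df): 88 patients"
- "Chi-squared test (5 df): 143 patients"
- "Student’s t-test: 102 patients"

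No second effect measure, sidedness or group ratio is named. The Statistical Analysis section adds only "A p-value <0.05 will be considered statistically significant", and says that continuous variables will be "analysed using Student’s t-test or the Wilcoxon test as appropriate". It describes no paired measurement.

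The section then sets the cohort at 500, states that this gives enough power for the primary and secondary outcomes and leaves room for exploratory and subgroup work, and adds: "This sample size also accommodates a potential dropout rate of up to 10" per cent. The Discussion calls the sample size calculation robust and relies on it for subgroup analyses.

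**The concern.** Cohen's d is a standardised difference between two means, so it fits the t-test bullet directly. It is not the usual input for a chi-squared test, for which Cohen's w is used. One d over all three bullets therefore needs checking, and 102 is very small for a standardised difference of 0.3.

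At stake is what a reader believes the cohort can show. The study aims to identify modifiable risk factors as well as to estimate incidence. Figures of 88 to 143 suggest that a subset of about 100 patients is enough to find an effect of the named size, and so that 500 leaves ample room for subgroups. If the figures belong to larger effects, that impression is wrong.

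**Working it through.** **Inputs.** d = 0.3, power 80%, α = 0.05, stated N of 102, 88 and 143, planned total 500 and dropout up to 10% all come from the Protocol article. My assumptions are two independent groups (no paired comparison is described), equal groups unless noted, and both one-sided and two-sided tests, since sidedness is not stated.

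**1. The chi-squared figures.** Power depends on the noncentrality λ = N·w². For 80% power at α = 0.05, λ = 7.849 with 1 df and 12.828 with 5 df.

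- 1 df: 7.849 / 0.3² = 87.2, rounded up to 88. Matches.
- 5 df: 12.828 / 0.3² = 142.5, rounded up to 143. Matches.

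Both figures are right for w = 0.3. For a balanced 2×2 table, d = 2w/√(1 − w²) = 0.6/√0.91 = 0.63, about twice the named effect. In the other direction, w = d/√(d² + 4) = 0.3/√4.09 = 0.148, and 7.849 / 0.148² gives about 357 (using the unrounded w). This conversion is direct only for 1 df, so I give no counterpart for 5 df.

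**2. The t-test figure.** Power comes from the noncentral t distribution with n₁ + n₂ − 2 df and noncentrality δ = d·√(n₁n₂/(n₁ + n₂)).

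| d | Sides | Per group | Total |
|---|---|---|---|
| 0.3 | two | 176 (175 gives 79.9%, 176 gives 80.1%) | 352 |
| 0.3 | one | 139 | 278 |
| 0.5 | two | 64 | 128 |
| 0.5 | one | 51 (50 gives 79.9%, 51 gives 80.6%) | 102 |

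Of these, only d = 0.5 one-sided returns a total of 102. Power at d = 0.3 with the stated number:

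- 102 in total (51 per group): 32% two-sided, 44% one-sided.
- 102 per group: 57% two-sided, 69% one-sided.

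A one-sided test at d = 0.35 gives 102 per group, but that is again not d = 0.3. A paired or one-sample two-sided test at d = 0.3 needs 90, or 90/0.9 = 100 with 10% dropout, which is close to 102 but not equal to it.

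**3. What the cohort gives at d = 0.3.** If the groups compared are hernia and no hernia, they will probably be unequal. The article states no expected incidence, so a range is needed. One can be back-solved from its precision figures, reading 5% as the half-width of the interval: p(1 − p) = n·0.05²/1.96².

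- n = 188: p(1 − p) = 0.122, p about 14%
- n = 255: p(1 − p) = 0.166, p about 21%
- n = 349: p(1 − p) = 0.227, p about 35%

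Two-sided power at d = 0.3, for the full cohort and after 10% dropout (500 × 0.9 = 450):

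| Share with hernia (assumed) | N = 500 | N = 450 |
|---|---|---|
| 14% | 64% | 60% |
| 21% | 78% | 73.5% |
| 35% | 89% | 86% |
| 50% (balanced) | 92% | 89% |

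**The case against.** The best defence is that the cohort does not rest on these bullets. The 500 exceeds all three figures, the largest precision figure (349) and the corrected balanced figure (352). With 450 evaluable patients and equal groups, two-sided power at d = 0.3 is 89%. The primary endpoints are incidences, and independent risk factors are assigned to logistic regression, so the t-test and chi-squared test play a supporting part. All of this stands, and it limits the severity.

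The paired-test explanation of 102 does not stand. No paired measurement is described, the dropout allowance is attached to the 500, and 88 and 143 carry no inflation.

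A reader might go further than the documents allow in three ways:

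- *That the cohort is too small.* At a 21:79 split, d = 0.3 needs 528 patients two-sided, more than 500. But the 21% is back-solved from one endpoint's precision figure and is not stated as a cohort-wide incidence, and hernia versus no hernia is a plausible comparison that the article does not spell out. At 35% the same cohort has 89% power.
- *That 102 contradicts the plan on sidedness.* The text states none, so there is nothing to contradict. The match with a one-sided test is an inference about where 102 came from.
- *That the 5 df figure has a specific corrected value under d = 0.3.* The conversion between d and w concerns two groups and has no direct meaning for a 5 df table.

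**Conclusion.** The concern holds as a mismatch between stated inputs and stated results. At d = 0.3 with two independent equal groups, the t-test needs 352 patients two-sided or 278 one-sided; neither choice rescues 102, which has less than 50% power as a total. The figures 88 and 143 are arithmetically right but carry the wrong label: they belong to w = 0.3, about twice the named effect in a balanced 2×2 table.

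The error does not by itself show that 500 is too small. Whether the cohort reaches 80% power at d = 0.3 for a continuous factor depends on the group split. Over the assumed incidence range it runs from 64% to 89% at N = 500 and from 60% to 86% at N = 450, against 92% and 89% with balanced groups. The general statements about power and subgroups should therefore not lean on the three bullets as written. This should be fixed, but it does not invalidate the design.

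**What to change.** In Sample Size Justification:

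1. Label 88 and 143 as based on Cohen's w = 0.3.
2. For the t-test, either keep d = 0.3 and state 352 in total (two-sided, equal groups), or keep 102 and state the effect size and sidedness on which it rests. The sponsor knows which was intended; the article does not show it.
3. State sidedness and group split for each test.
4. Add power at d = 0.3 over an assumed range of hernia incidence, at 500 and at 450 patients, as in the last table of the working, and mark the incidences as assumptions.
5. Limit the statements on sufficient power and subgroup analyses, here and in the Discussion, to what those figures support.

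The cost is wording only. No extra patients are needed, though the stated figures become less favourable.

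### The chi-squared sample sizes of 88 and 143 are those for Cohen's w = 0.3, not the stated Cohen's d = 0.3, and the t-test figure of 102 does not follow from d = 0.3 either

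*Protocol article*

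**What the plan says.** In the protocol article, Sample Size Justification, a single effect size introduces three required sample sizes: "To detect a moderate effect size (Cohen’s d = 0.3) with 80% power at α = 0.05". The list under it reads "Chi-squared test (1 df): 88 patients", "Chi-squared test (5 df): 143 patients" and "Student’s t-test: 102 patients".

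The section then sets the cohort at 500 patients, says that this number "ensures sufficient power to assess primary and secondary outcomes", and allows for up to 10% dropout. The Statistical Analysis section makes chi-squared the test for categorical variables ("Categorical variables will be compared using the Chi-squared test") and sets the threshold: "A p-value <0.05 will be considered statistically significant".

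The section does not mention Cohen's w, a conversion from d to w, a group ratio, the sidedness of the t-test, or the table to which the 5-df test would apply.

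**The concern.** Cohen's d is a standardised difference between two means. The effect measure of a chi-squared test is Cohen's w, for which the noncentrality is N × w². The two scales differ: for two equal groups, d = 0.3 is roughly w = 0.15, and halving w quadruples the required N. One d therefore cannot serve for all three lines without a conversion.

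What is at stake is how the results will be read. Many of the factors named in the hypotheses and in Data Collection are categorical (closure technique, suture material, NPWT, binders). A reader who takes d = 0.3 at face value would think that 88 or 143 patients suffice to detect a fairly small difference, and might read a null chi-squared result accordingly. The effect actually sized is about twice as large on the w scale.

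**Working it through.** **Inputs from the protocol article:** effect 0.3 (labelled d), power 80%, α = 0.05, stated N of 88, 143 and 102, cohort 500, dropout up to 10%. Evaluable patients: 500 × 0.9 = 450.

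**Step 1. Reproduce the chi-squared figures.** The noncentrality that gives 80% power at α = 0.05 is 7.849 for 1 df and 12.828 for 5 df. N = noncentrality / w².
- w = 0.3, 1 df: 7.849 / 0.09 = 87.2, so 88 (power 80.4%).
- w = 0.3, 5 df: 12.828 / 0.09 = 142.5, so 143 (power 80.2%).

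Both match the plan exactly. Relaxing α to 0.10 does not (69 and 117 at w = 0.3).

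**Step 2. Take d = 0.3 literally.** Assume two equal groups; the plan gives no ratio. Then w = d / √(d² + 4) = 0.3 / √4.09 = 0.1483, and w² = 0.0220.

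| | 1 df | 5 df |
|---|---|---|
| N for 80% power | 7.849 / 0.0220 = 357 | 12.828 / 0.0220 = 583 |
| Power at the stated N | 28.5% (N = 88) | 23.2% (N = 143) |
| Power at N = 450 | 88.2% | 67.2% |
| Power at N = 500 | 91.3% | 72.6% |

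N is computed from unrounded w. The shortcut w = d/2 = 0.15 gives 349 and 571. The result depends on the split: 424 and 692 at 30:70, 553 and 904 at 20:80. The 5-df column carries a two-group conversion over to a larger table, so it is illustrative only.

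**Step 3. Check the t-test line, where d is the right measure.**
- d = 0.3, two-sided, two equal groups: 176 per group, 352 in total.
- d = 0.3, one-sided: 139 per group, 278 in total.
- d = 0.3, paired or one-sample, two-sided: 90.
- d = 0.5, one-sided: 51 per group, 102 in total (power 80.6%).

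None of the d = 0.3 versions gives 102. At d = 0.3 two-sided, 102 patients in total (51 per group) have 32% power, and 102 per group have 57%.

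**Step 4. What w = 0.3 means as a hernia risk.** Assume incidence p = 0.21 and exposed fraction q = 0.5. Neither is stated in the plan; 21% is a value that reproduces its precision figure of 255, since 1.96² × 0.21 × 0.79 / 0.05² = 254.9. The risk difference is w × √[p(1 − p) / (q(1 − q))] = w × √(0.1659 / 0.25) = w × 0.8146.
- w = 0.3: difference 24.4 points, 33.2% versus 8.8%, risk ratio about 3.8.
- w = 0.1483: difference 12.1 points, 27.0% versus 15.0%.

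**Step 5. What 450 evaluable patients can detect with 80% power.**
- 1 df: w = √(7.849 / 450) = 0.13, or 26.4% versus 15.6% on the step 4 assumptions.
- 5 df: w = √(12.828 / 450) = 0.17.

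**The case against.** The strongest reply is that this is a slip in a label. An exact match on both lines shows that the calculation used w. For w = 0.3 the 80% power is correct, and 500 patients give more than 99.9% for both tests. That stands, and it limits the consequence.

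A reader might infer that the stated power is simply wrong and that the 5-df comparison is underpowered even with the whole cohort. The document does not support that. The shortfall appears only if d = 0.3 was the true target, and only under an equal-group conversion that the plan does not give and that has no unique meaning for a 5-df table. For two-category comparisons, even the literal reading is met with equal groups: 88% power in 450 patients.

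A reader might also infer that 500 was derived from the two chi-squared lines. The text does not say so. The section opens with precision targets, the largest being 349 for parastomal hernia. The primary endpoints are incidences with confidence intervals, and independent risk factors are to come from logistic regression.

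Finally, the risk translation is not needed to correct the label, and it rests on an incidence and an exposure split that the plan does not state. That is fair: it illustrates the size of the effect and proves nothing about the plan.

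None of this rescues the sentence as printed. On either reading of 0.3, the effect size and the chi-squared sample sizes do not belong together, and relabelling those lines leaves the t-test line unexplained.

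**Conclusion.** The concern holds as a misstated power basis. The figures 88 and 143 belong to w = 0.3, which for two equal groups is equivalent to d = 2 × 0.3 / √(1 − 0.09) = 0.63, about twice the printed value. The figure 102 does not follow from d = 0.3 in any version checked; it fits d = 0.5 one-sided. One label therefore covers at least two different effects, and the value it states produces none of the three figures.

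The match at w = 0.3 is certain, because both lines reproduce to the patient. The literal-reading figures (357 and 583 patients; 29% and 23% power) are conditional on d = 0.3 being the target and on two equal groups. They show how much the label matters and do not demonstrate a deficit in the cohort. The sufficient-power sentence is too broad as it stands, because it names no effect and the effect sizes printed above it are mislabelled.

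**What to change.** Reword the power paragraph of Sample Size Justification:
- For the two chi-squared lines, name the effect as Cohen's w = 0.3. The figures 88 and 143 then stand.
- Give the t-test line its own d, sidedness and group ratio, and recalculate N. If d = 0.3 two-sided with equal groups is meant, the figure is 352 in total. If 102 is kept, state the effect and sidedness that produce it.
- Limit the sufficient-power sentence to effects that about 450 evaluable patients can detect with 80% power: w = 0.13 for 1 df and w = 0.17 for 5 df.
- If any of these is translated into hernia risk, state the assumed incidence and exposure split beside it.

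The cost is one paragraph. Enrolment, endpoints and analyses do not change. The t-test figure becomes less favourable if d = 0.3 two-sided is kept.
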